### Statistical Methods and Data Analysis

The full analysis set (FAS) will include all patients randomized to the trial, regardless of compliance. The PPS will include all patients from the FAS, who had a 12-week post-intervention visit and who complied with their assigned treatment.

The primary analysis will be done on the FAS and based on the intention to treat principle. Patients will be analyzed according to the group to which they were assigned. Missing values in the primary endpoint will be imputed using multiple imputations via chained equations based on baseline characteristics. An ANCOVA approach will be taken: a linear regression model will be used to model patient VO_2peak_ at post-intervention as outcome, with the baseline value as an independent covariate. As an explorative analysis, the association of tHb-mass and patient type, as well as their combined effects on VO_2peak_ will be examined using multiple regression models or other methods for estimating causal effects. As a safety analysis, the number and type of AEs will be summarized and reported per group. In addition, the number of non-compliant patients and their baseline characteristics compared between treatment groups will be summarized.

Confounding variables such as baseline patient characteristics (e.g., age, BMI, smoking/drinking), comorbidities, medication, and baseline fitness level will be accounted for during regression analyses.

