### Sample Size

We use a closed form formula to assess the sample size, as implemented in the R function “power.t.test()”. This provides us a sample size for comparison of two independent groups. Borm et al. (2007) showed that including the baseline value as a covariate in an ANCOVA design as planned here, can reduce the required sample size while maintaining power. Accordingly, the required sample size would be N_total_ = N_t−test_
^*^ (1 – ρ^2^) + 2, where ρ is the within patient correlation between baseline values and follow-up. To obtain realistic assumptions on the baseline VO_2peak_ distribution required for the sample size calculation, we performed a meta-analysis of five research papers (Kitzman et al., 2010, 2013; Edelmann et al., 2011; Alves et al., 2012; Smart et al., 2012). The fixed effects meta-analysis suggested the standard deviation of VO_2peak_ at baseline to be 3.39 ml min^−1^ kg^−1^. For the sample size estimation, we take a slightly more conservative value, assuming baseline VO_2peak_ to have a standard deviation of 4.2 ml min^−1^ kg^−1^, ~25% higher than suggested by the meta-analysis. In addition, we assume the within-patient correlation to be 0.7 ml min^−1^ kg^−1^, which is rather low for such measurements. We set the type-I error rate, α, to 0.05, and the power of the study (1-β) to 80%. We only allow a dropout rate of 10% for the primary outcome at 12 weeks.

Under these assumptions, with a 1:1 treatment allocation ratio, 86 patients need to be recruited in order to show a minimal clinically relevant difference of 2 ml min^−1^ kg^−1^, while maintaining power for the PPS with 77 evaluable patients.

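### The stated basis for imputing 12-week VO2peak does not include randomised arm; followed literally, it shrinks the primary HIT–MCT difference by about the missing fraction

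*Protocol article*

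**What the plan says.** The point rests on three statements in the protocol article, Statistical Methods and Data Analysis.

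- On the population: "The primary analysis will be done on the FAS and based on the intention to treat principle", followed by "Patients will be analyzed according to the group to which they were assigned". The FAS holds every randomised patient, so imputed values enter the primary result.
- On missing data: primary-endpoint values will be "imputed using multiple imputations via chained equations based on baseline characteristics". No other predictor is mentioned, and neither is imputation within arm.
- On the model: "a linear regression model will be used to model patient VO_2peak_ at post-intervention as outcome, with the baseline value as an independent covariate". The arm term is not spelled out here either, although the analysis is a comparison of the assigned groups.

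The Sample Size section gives the expected loss: "We only allow a dropout rate of 10% for the primary outcome at 12 weeks".

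**The concern.** An imputation model should contain at least the terms of the analysis model it feeds, and above all the term being estimated. Here that term is randomised arm. In the article's own usage, arm is not a baseline characteristic. The Statistical Methods section compares the baseline characteristics of non-compliant patients between treatment groups, and its examples of such characteristics are age, BMI and smoking or drinking.

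A statistician who follows the sentence would therefore predict missing 12-week VO2peak from baseline data pooled over both arms. A HIT patient and an MCT patient with the same baseline would receive imputed values from the same distribution. The ANCOVA would then estimate a between-arm difference from data in which the imputed part has none. At stake are the size of the primary estimate and the power of the primary analysis.

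**Working it through.** **Inputs, all from Sample Size:** 86 recruited, 1:1; difference δ = 2 ml/min/kg; SD 4.2; baseline/follow-up correlation 0.7; α = 0.05 (sidedness not stated, two-sided assumed); power 80%; dropout 10%, taken as the missing fraction m.

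**1. The plan's own figure.** The t-test calculation gives 70.2, so 71 per arm and 142 in total. The ANCOVA reduction gives 142 × (1 − 0.7²) + 2 = 142 × 0.51 + 2 = 74.4, so 75. Rounding each arm up instead gives 71 × 0.51 + 1 = 37.2, so 38 per arm and 76 in total. Dividing by 0.9 gives 84 to 85 after rounding up, or 86 if made even, and 86 × 0.9 = 77.4. The stated 86 and 77 are reproduced to within two patients.

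**2. Expected attenuation without arm.** Take equal arms with the same m in each, and outcomes missing completely at random. At a given baseline, the pooled imputation model predicts a value halfway between the arms, that is δ/2 above the MCT mean. Relative to that MCT mean:

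- HIT: (1 − m)δ + m·δ/2
- MCT: m·δ/2
- Difference: (1 − m)δ

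At m = 5%, 10% and 20% this is 1.9, 1.8 and 1.6 ml/min/kg.

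**3. Standard error.** The residual SD is 4.2 × √0.51 = 3.00. With 77 observed patients the standard error of the difference is 3.00 × √(4/77) = 0.68. The no-arm estimator behaves roughly like (1 − m) times the observed-case estimator, so its true SD is about 0.9 × 0.68 = 0.62. Rubin's rules add between-imputation variance as if the imputed values were independent information about the arm contrast. In simulation they report about 0.70, against an empirical SD of 0.61 to 0.65.

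**4. Simulation.** N = 86, 20 imputations from a normal linear model, ANCOVA, Rubin's rules with small-sample degrees of freedom, 1,500 to 3,000 trials per scenario. Ranges are over separate runs.

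| Missing | True difference | Arm in imputation model | Mean estimate | Rejection rate |
|---|---|---|---|---|
| 10% | 2.0 | no | 1.79–1.82 | 74–76% |
| 10% | 2.0 | yes | 2.00–2.03 | 81–83% |
| 20% | 2.0 | no | 1.60–1.61 | 58–59% |
| 20% | 2.0 | yes | 2.00–2.02 | 76–78% |
| 5% in one arm, 15% in the other | 2.0 | no | 1.81 | 75% |
| 5% in one arm, 15% in the other | 2.0 | yes | 2.02 | 82% |
| 10% | 0 | no | 0.00 | 2.4% |
| 10% | 0 | yes | 0.00 | 4.4% |

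A further check with 10,000 trials agreed. With a 10% chance of missingness per patient it gave 1.81 and 75% without arm, and 2.01 and 82% with it. With exactly 9 of 86 values missing (10.5%) it gave 1.78 and 73% against 1.99 and 81%. The 20% rows go beyond the plan's dropout assumption and only show how the effect scales.

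**The case against.** The strongest reply is that the article never says baseline data alone will be used and never excludes arm. It is a condensed account, and the full protocol or an analysis plan may list the predictors. The neighbouring ANCOVA sentence also leaves arm unnamed, yet nobody would conclude that the primary model has no treatment term.

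Part of this stands. A reader might infer that the trial has decided to leave arm out, and the text does not support that. The parallel with the ANCOVA sentence is weaker than it looks, however. A two-group ANCOVA analysed by assigned group implies an arm term, and nothing comparable implies one in the imputation model. There the article does state a basis, and by its own usage that basis does not cover arm. This is a stated rule that reads badly, not detail left to another document.

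Three further replies are fair:

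- A reader might infer that the power claimed in Sample Size is contradicted. That section ties its explicit statement to the per-protocol set of 77 evaluable patients, and that set requires a 12-week visit. The loss computed here belongs to the imputed FAS, for which no separate power is stated.
- A reader might say that the imputed values contain no treatment effect at all. They contain the average outcome of both arms; what they lack is a difference between arms.
- The 2.0 is assumed to hold for patients who leave as well. Concomitant Treatments removes patients whose ability to exercise is affected by worsening heart failure or new disease, and their difference under intention to treat need not be 2.0. The exact bias for the real target is therefore not established; the figures hold under missing completely at random.

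**Conclusion.** The point holds in a limited form. As written, the imputation basis does not include randomised arm. Followed literally, it lowers the expected primary estimate from 2.0 to about 1.8 ml/min/kg at 10% missing and costs about 7 percentage points of FAS power. This assumes outcomes missing completely at random, the Sample Size inputs, and two-sided testing at 0.05.

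The size is modest at the planned dropout and grows in proportion to the missing fraction. The direction is conservative: with no true difference the rejection rate is about 2.4%, so a false claim of benefit does not become more likely. The risk is an understated difference or a missed one. It does not invalidate the design, but it should be corrected because the primary endpoint depends on it and the correction is trivial.

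**What to change.** Amend the imputation sentence to the following effect: *missing 12-week VO2peak will be handled by multiple imputation via chained equations, done separately by randomised arm (or with randomised arm in the imputation model), based on baseline characteristics including baseline VO2peak and sex.* Baseline VO2peak is the ANCOVA covariate and sex is the stratification factor, so both belong in the model.

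The number of sessions attended may be added as an auxiliary predictor. It must exist, because the per-protocol set is defined by 29 sessions. Training workload should be added only if it is recorded; the article says workload is adjusted during training but not that it is stored as trial data. Neither addition is needed to remove the problem.

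The cost is one phrase of wording. Arm and the baseline values are already held, so no new data are needed, and naming arm has no material downside.

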### Randomization

Patients will be randomly allocated to either the intervention or the control group in a 1:1 ratio stratified by gender. Randomization will be done using a computer-based system implemented in the Castor software (Castor, Amsterdam, Netherlands). The randomization procedure includes a minimization algorithm. The randomization procedure is implemented in the online electronic-data-capture system provided by Castor. Only authorized study personnel will have access to the randomization tool and can assign a treatment to a new study patient. Due to the minimization algorithm, the allocation sequence is totally concealed until randomization is carried out.

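### Allocation is stratified by gender but the primary ANCOVA does not name it, and an open list of confounders leaves the primary model not uniquely fixed

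*Protocol article*

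**What the plan says.** - **Allocation.** The Randomization section assigns patients to "either the intervention or the control group in a 1:1 ratio stratified by gender", through a procedure that includes minimisation. No balancing factor other than gender is named.
- **Primary model.** Statistical Methods and Data Analysis specifies a linear regression of post-intervention VO2peak "with the baseline value as an independent covariate", run on the full analysis set with multiple imputation of missing outcomes. Gender is not mentioned.
- **Further covariates.** The last sentence of the same section reads: "Confounding variables such as baseline patient characteristics (e.g., age, BMI, smoking/drinking), comorbidities, medication, and baseline fitness level will be accounted for during regression analyses". Gender is not in this list either. The items are given as examples, no selection rule is stated, and the sentence does not say which regressions it governs.
- **Sizing.** The Sample Size section assumes ANCOVA with the baseline value as the covariate, and no other adjustment.

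**The concern.** Two things are at stake.

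1. **The stratification factor.** When allocation is forced to be balanced on a factor, chance imbalance in that factor no longer contributes to the error of the treatment comparison. A model without the factor still leaves its variance in the residual. The reported standard error then overstates the real uncertainty, and the test rejects less often than its nominal level.

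2. **A single primary result.** The primary analysis is itself a regression, so the confounder sentence can be read as reaching it. On that reading the primary estimate depends on which covariates are eventually chosen from a list that is not closed, and the model is no longer the one used for sizing. Unlike the patient characteristics, medication is not clearly tied to baseline. The Concomitant Treatments section allows medication during the trial, so adjustment for something that changed after randomisation is not excluded.

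**Working it through.** **Inputs (Sample Size section).** Two-sided α 0.05 (sidedness is not stated; two-sided is the default of the R function the article names), power 80%, difference 2, SD 4.2 (all in ml/min/kg), dropout 10%, and "we assume the within-patient correlation to be 0.7".

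**Step 1: the plan's own sample size.**
- Two-sample t-test: 70.2, so 71 per arm.
- ANCOVA reduction per arm: 71 × (1 − 0.7²) + 1 = 37.2, so 38.
- Dropout: 38 / 0.9 = 42.2, so 43 per arm and **86 in total**. Evaluable: 86 × 0.9 = 77.4, so 77.

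The stated 86 and 77 are reproduced with baseline-only adjustment. Rounding only the t-test size gives (142 × 0.51 + 2) / 0.9 = 82.7, so 83; the 86 comes from rounding up per arm at each step.

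**Step 2: power of the baseline-only model.** Residual SD = 4.2 × √0.51 = 3.00. With 77 patients, SE = 3.00 × √(4/77) = 0.684 and power is 82.3%.

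**Step 3: adding gender.** Let R² be the share of that residual variance explained by gender. The article gives no value, so 0.02 to 0.10 is an assumption. The reported SE becomes 0.684 × √(1 − R²).

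| Assumed R² | SE with gender | Change in SE | Power with gender |
|---|---|---|---|
| 0.02 | 0.677 | −1.0% | 83.1% |
| 0.05 | 0.666 | −2.5% | 84.2% |
| 0.10 | 0.649 | −5.1% | 86.1% |

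Against 82.3%, the gain is 0.8, 1.9 and 3.8 points.

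**Step 4: simulation.** 76 patients, half of them women (an assumption), arms split evenly within gender, 15,000 trials per scenario. Each cell shows the model without gender / with gender.

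| Assumed R² | True SE | Reported SE | Type I error | Power |
|---|---|---|---|---|
| 0.02 | 0.677 / 0.677 | 0.691 / 0.684 | 4.6% / 4.7% | 81.8% / 82.3% |
| 0.05 | 0.674 / 0.673 | 0.690 / 0.672 | 4.7% / 5.3% | 81.9% / 83.2% |
| 0.10 | 0.658 / 0.658 | 0.693 / 0.656 | 3.9% / 5.0% | 82.5% / 85.4% |

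The true SE is the same with or without gender, and the mean estimate stays at about 2.00. Only the reported SE and the rejection rates move. Simulation error on a type I rate near 5% is about √(0.05 × 0.95 / 15,000) = 0.2 points, so differences at the smaller R² values are close to noise. The simulated power gain (0.5 to about 3 points) is a little below Step 3, because the true SE also falls when balanced gender explains variance.

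**Step 5: the open list.** Take gender, age, BMI, smoking, drinking, comorbidities and medication as one optional term each, with baseline VO2peak always included. That gives 2⁷ = 128 candidate models. Under no treatment effect (76 patients, 2,000 trials):

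| Assumed R² per covariate | Baseline-only model, p < 0.05 | At least one of 128 models, p < 0.05 | Median spread of the estimate (ml/min/kg) |
|---|---|---|---|
| 0 | 5.0% | 8.3% | 0.31 |
| 0.02 | 4.9% | 10.5% | 0.50 |
| 0.05 | 4.5% | 15.8% | 0.76 |

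The last row lets the seven covariates together explain 7 × 0.05 = 35% of the residual variance, which is a strong assumption. The target difference is 2.

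**The case against.** Several points on the other side have force.

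- **Precision.** A reader might infer that omitting gender makes the estimate less precise. Step 4 shows otherwise: the true SE is unchanged. The error is in the conservative direction, and the stated power is met without gender.
- **Size.** Baseline VO2peak per kg should already absorb much of any difference between the sexes. At a partial R² of 0.02 the effect is negligible. A share of 0.20 would push type I error to about 3%, but nothing in the article supports so large a value.
- **Contradiction.** A reader might take the confounder sentence as flatly contradicting the one-covariate model. It stands in its own paragraph and may be meant for the exploratory haemoglobin-mass regressions, where talk of confounding fits better. Its scope is unclear, which is an ambiguity and not a contradiction.
- **The two halves pull apart.** If the open list does reach the primary model, gender could be included as a patient characteristic. Its omission is certain only on the baseline-only reading.
- **Double counting.** One might infer that the fitness item enters baseline VO2peak twice. The article never equates the two, and a duplicated regressor would be redundant without distorting the treatment effect. The item is undefined, no more.
- **Worst case.** The 8% to 16% requires trying every subset and keeping the smallest p-value. Analysts are to be blinded to allocation, which limits steering towards a favoured arm. It does not prevent selection on a two-sided p-value, which is the same whichever coded arm is which.
- **Condensed article.** A final covariate list is often left to the analysis plan. Here, however, the article states the primary model and then adds a general sentence that may alter it, so the lack of clarity is in the text itself.

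**Conclusion.** The point holds in limited form, and neither part threatens the design.

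On the baseline-only reading, the primary model leaves out the stratification factor. The consequence is a reported SE about 1% to 5% too large, about 1 to 4 power points lost, and a type I error of about 3.9% at the upper end. This rests on an assumed partial R² of 0.02 to 0.10 and on the article's own SD and correlation. There is no bias, no loss of true precision and no shortfall against 80% power.

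On the wider reading, the primary model is not uniquely fixed. The 8% to 16% false-positive rate is what unrestricted selection could produce, not a prediction of what the analysts will do. The spread of 0.31 to 0.76 ml/min/kg across models is enough to matter for a borderline result.

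Either reading leaves something to repair, and one clarification settles both.

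**What to change.** - State one primary model: 12-week VO2peak on arm, baseline VO2peak and gender, plus any other factor used in the minimisation. Use it in both the full analysis set and the per-protocol set.
- Include gender in the imputation model.
- Say explicitly that the confounder sentence does not apply to the primary model.
- Limit further covariates to one sensitivity analysis with a closed list of variables measured at baseline. If the fitness item is kept, define it.

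The cost is wording and one degree of freedom. The recruitment target of 86 and the conduct of the trial are unaffected.

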### Data Collection, Management, and Retention

Data will be anonymized and stored in a pseudonymized manner by using the patient IDs. Personal data and contact information for the follow-up phone calls and assessment of physical activity will be entered into a separate excel file with restricted access for staff performing these calls. Collection and management of the clinical trial data will be done using an electronic data capture (EDC) system based on the software Castor. Source data, randomization and pseudonymization lists will be kept under lock and key. Password protection ensures that only authorized persons can enter the system to view, add or edit data according to their permissions. The EDC system will be locked after all data have been monitored and all raised queries have been resolved. Data will be archived at the DSBG. Independently from investigators, regulatory authorities can audit this trial. Direct access to source documents will be permitted for purposes of monitoring, audits and inspections. All involved parties must keep the participant data strictly confidential. Any results of this study will be published in an anonymized manner. The study protocol and dataset shall be accessible to any regulatory authority after publication for at least 10 years.

## Discussion

Heart failure, in particular heart failure with preserved ejection fraction (HFpEF) constitutes a large and increasing burden to the national and international healthcare systems. Nevertheless, the etiology of HFpEF has not yet been fully understood and symptoms are often misdiagnosed. Since mortality in patients with HFpEF remains unacceptably high with a 5-year survival rate of only 30%, new therapeutic strategies are urgently needed (Burkhoff, 2012; Meta-Analysis Global Group in Chronic Heart, 2012; Lam et al., 2018). Maximum oxygen uptake (VO_2peak_) as a measure for exercise capacity is a strong and independent predictor of morbidity and mortality in patients with HFpEF, but few data are available on the efficacy of training programs (Fukuta, 2020). A study of Angadi et al. (2015) found that HIT significantly better improved VO_2peak_ and left ventricular diastolic dysfunction in HFpEF patients compared to MCT. They also demonstrated that HIT was well-tolerated in this cohort consisting predominantly of female older and overweight or even obese individuals. The study of Donelli Da Silveira et al. (2020) (*n* = 19, 12-week duration) that investigated a relatively young sample (mean age: 60 years) with few comorbidities supports these findings. However, in OptimEx, the largest study conducted in HFpEF patients to date comparing MCT vs. HIT, HIT was not superior over MCT (Mueller et al., 2021; Pandey and Kitzman, 2021). However, the results of OptimEx should be interpreted with caution. Patients in the MCT group completed five training sessions per week compared to three training sessions in the HIT group and training modalities were not balanced between groups with regards to energy consumption, considerably limiting the generalizability of the results. These findings are supported by a recent meta-analysis (Fukuta et al., 2019). Besides the effects on the cardiopulmonary system, training directly affects the skeletal muscle (Hoppeler et al., 1985, 2011; Fukuta et al., 2019). Results from a recent study indicate that resistance training - even as a single intervention - can increase muscle strength, aerobic capacity and QoL in patients with HF (Giuliano et al., 2017). Furthermore, a not-too-strenuous aerobic training may be better suited for subjects at low training states such as HFpEF patients because of better coping with low aerobic training stimuli (Schindler et al., 2019) – as e.g., in the beginning of our training regime. Introducing strength training at the beginning might not only allow to prepare skeletal muscle to adapt to a constantly improving cardiopulmonary system, but also to start with a lower aerobic stimulus, while still having a reasonable total stimulus per training unit (Fluck et al., 2017; Fitze et al., 2019). In consequence, a combination of strength and endurance training might be better suited for patients with HFpEF (Ponikowski et al., 2016; Schindler et al., 2019).

Our analyses of biomarkers reflect the most important pathogenetic pathways, will provide further important insights into the pathophysiology of HFpEF, and might be helpful in predicting the response to exercise therapy in order to effectively guide risk stratification as well as preventive and therapeutic measures.

